## Abstract

**Background:**

Patients with type 2 diabetes mellitus (T2DM) struggle with the management of their condition due to difficulty relating lifestyle behaviors with glycemic control. While self-monitoring of blood glucose (SMBG) has proven to be effective for those treated with insulin, it has been shown to be less beneficial for those only treated with oral medications or lifestyle modification. We hypothesized that the effective self-management of non-insulin treated T2DM requires a behavioral intervention that empowers patients with the ability to self-monitor, understand the impact of lifestyle behaviors on glycemic control, and adjust their self-care based on contextualized SMBG data.

**Objective:**

The primary objective of this randomized controlled trial (RCT) is to determine the impact of *bant2*, an evidence-based, patient-centered, behavioral mobile app intervention, on the self-management of T2DM. Our second postulation is that automated feedback delivered through the mobile app will be as effective, less resource intensive, and more scalable than interventions involving additional health care provider feedback.

**Methods:**

This study is a 12-month, prospective, multicenter RCT in which 150 participants will be randomly assigned to one of two groups: the control group will receive current standard of care, and the intervention group will receive the mobile phone app system in addition to standard of care. The primary outcome measure is change in glycated hemoglobin A1c from baseline to 12 months.

**Results:**

The first patient was enrolled on July 28, 2015, and we anticipate completing this study by September, 2018.

**Conclusions:**

This RCT is one of the first to evaluate an evidence-based mobile app that focuses on facilitating lifestyle behavior change driven by contextualized and structured SMBG. The results of this trial will provide insights regarding the usage of mobile tools and consumer-grade devices for diabetes self-care, the economic model of using incentives to motivate behavior change, and the consumption of test strips when following a rigorously structured approach for SMBG.

**Trial Registration:**

ClinicalTrials.gov NCT02370719; https://clinicaltrials.gov/ct2/show/NCT02370719 (Archived at http://www.webcitation.org/6jpyjfVRs)

## Introduction

### Background

The increasing global prevalence of diabetes is challenging traditional approaches towards diabetes management. It is not sustainable, nor cost effective, to assume that there will be an increase in health care delivery resources to address the growing prevalence of diabetes. Novel self-management tools, which aim to engage patients in daily diabetes care and optimize the role of health care professionals, may facilitate a more robust, scalable, and effective approach to the management of diabetes [1].

While self-management is a major component of chronic disease management, the majority of patients are not provided, or do not have access to, the tools and personalized education needed to engage in daily self-care practices [2] *.* Self-monitoring of blood glucose (SMBG) continues to be prescribed to patients as a self-management tool without the additional context, education, and frequent feedback required to interpret trends and adjust behaviors accordingly [3,4].

Furthermore, recent policy changes have reduced the reimbursements for test strips for patients who are not treated with insulin, further limiting access to SMBG as a self-monitoring tool [3]. These policy changes have been informed by evidence that evaluated SMBG as a standalone intervention, without the training required to understand the results of SMBG or frequent feedback from health care providers (HCPs). As such, patients that are not treated with insulin have limited support for test strip reimbursements, and also lack the education and tools needed to interpret and derive actionable knowledge from SMBG data.

Recent evidence has shown that when SMBG is performed in a structured manner, and is coupled with appropriate feedback and education, it may lead to positive health behavior change amongst patients with type 2 diabetes mellitus (T2DM) who are not treated with insulin [3]. As such, we hypothesized that the effective self-management of non-insulin treated T2DM requires a behavioral intervention that empowers patients with the ability to self-monitor, understand the impact of lifestyle behaviors on glycemic control, and adjust their self-care based on contextualized data.

The popularity of smartphones has presented an opportunity to deliver this type of intervention in the form of an evidence-based and user-centered diabetes self-management app [5-8]. The systematic design of the mobile health (mHealth) app *bant2* was informed by evidence and feedback from end-users, and is following a rigorous evaluation framework [1]. The evaluation framework is a blended model of the Knowledge to Action and Medical Research Council’s framework for complex interventions, and ensures that the intervention and study design, as well as the evaluation, follow a robust methodological approach [9].

The primary objective of this randomized controlled trial (RCT) is to determine the impact of the evidence-based, patient-centered, mobile app for the self-management of T2DM. Although there are many diabetes-focused electronic health (eHealth) tools currently available, the majority require a third party HCP to facilitate decision making [5]. Our second postulation is that automated feedback delivered through the mobile app will be as effective, less resource intensive, and more scalable than interventions involving additional HCP feedback.

## Methods

### Trial Design

The *bant2* study is a 12-month, prospective, multicenter, unblinded, parallel RCT in which 150 participants are randomly assigned to one of two groups: the control group receives current standard of care, and the intervention group receives the mobile phone app system in addition to standard of care. During the study period, all participants (intervention and control) attend quarterly clinic visits (standard care) and receive usual care.

The primary recruitment strategy for this study is through self-referral at primary care and community practices throughout the Greater Toronto Area. This area includes sites that are situated in urban and suburban settings. The University Health Network Research Ethics Board (REB) approved the study (14-7978-AE). Local institutional REB approvals were also obtained from the following participating sites: St. Joseph’s Health Care Centre (#2015-010), Trillium Health Partners (#698), and North York General (#15-0038). For sites without an institutational REB, namely the Taddle Creek Diabetes Education Program and LMC Diabetes and Endocrinology, approval was obtained from an Institutional Review Board (Pro00016415).

Randomization is being conducted at the patient level, using random block sizes of four and six to reduce the variance across the entire sample, with a 1:1 allocation ratio. Stratificaiton is also conducted by recruitment site. The allocation envelopes contain a piece of paper with either *control* or *intervention* written upon it, as well as a random patient identifier. The study coordinator allocates each participant by taking the envelope on the top of the stack, and enrolls the participant into the appropriate study arm, as indicated.

### Intervention

The participants randomly assigned to the intervention group will receive an iPhone 5S loaded with the *bant2* app, as well as a Bluetooth-enabled (a standard protocol for short distance wireless communication) Wahoo weight scale (Wahoo Fitness, Atlanta, GA, USA), a Jawbone UP24 (Jawbone, San Francisco, CA, USA) wrist-worn activity monitor, and a Jazz blood glucose meter (Agamatrix, Salem, NH, USA) [9]. We will also provide BlugluLe, a Bluetooth adapter that connects to the glucose meter and enables the wireless transfer of readings from the meter to the iPhone. The *bant2* mobile app also enables users to capture meal photos using the built-in camera, and track medication adherence on a weekly basis. In addition to the wrist-worn activity monitor, steps could also be tracked through the mobile phone itself using the built in accelerometer.

The *bant2* app, shown in Figure 1, facilitates self-monitoring of lifestyle behaviors, and enables patients to correlate their lifestyle behaviors with their glycemic control through paired (pre- and post-prandial) blood glucose testing [10]. Upon data capture, the app will assess the other data points in context, identify positive and negative behaviours based on the analysis, and faciliate remedial decision making. The app also enables patients to set goals and receive reminders, participate in a closed-gated social community, and accumulate points for positive behaviors, which can be redeemed for tangible gift cards (eg, groceries, gym memberships) [9]. This app builds on a previous version of the *bant* app, which focused on engaging adolescents in the self-management of type 1 diabetes mellitus (T1DM). A 12-week pilot of *bant* app demonstrated positive behavior change amongst the adolescents with T1DM [11].

We have ensured that all of the appropriate safeguards are in place to protect personal health information. For example, the iPhone requires a passcode to access the app, and the app itself requires a username and password. In the event that the device is lost or stolen, we can remotely wipe the device using mobile data management software (Airwatch, Atlanta, GA). The *bant2* app is intended to provide guidance and facilitate diabetes self-management, and is not classified as a medical device. Given that the app poses minimal risk to the patient, Health Insurance Portability and Accountability Act requirements do not apply.

**Figure 1 figure1:**
[figure not shown]
The bant2 mobile app enables users to monitor lifestyle behaviors and correlate them to their overall glycemic control.

### Participants

The inclusion criteria for participants include: definitive diagnosis of T2DM, not treated with insulin, at least 18 years of age, a baseline glycated hemoglobin A1c (A1c) of 7.5% or higher, and ability to speak and read English.

Exclusion criteria include: inability to use a mobile phone (eg, due to vision problems) or to comply with home monitoring (eg, due to suffering from anxiety or depression), and duration of diabetes under one year. Participants who have had diabetes for less than one year are excluded because they typically demonstrate a higher adherence to self-care and have high levels of motivation [12].

### Outcomes

The primary outcome measure is change in A1c from baseline to 12 months. Each recruitment site is provided with a DCA Vantage Analyzer (Siemens, Munich, Germany) point of care A1c device to reduce the variability in the A1c laboratory assays. As secondary end points, A1c measurements are also collected at 3-month intervals (3, 6, and 9 months). Clinical staff within the patient’s circle of care are conducting the point of care A1c tests.

Secondary outcomes include blood pressure (mmHg), weight (pounds), total cholesterol (mmol/L), Low Density Lipoprotein cholesterol (mmol/L), and weight at baseline, 3, 6, 9, and 12 months. The number of participants who achieve optimal glycemic control (A1c <7%), as well as the type and frequency of medication changes, will also be measured. Furthermore, validated instruments described in Table 1 are being used to collect and measure burden of disease and diabetes-related self-efficacy and self-care, pre-, mid-, and post-study.

**Table 1 table1:** Validated instruments administered pre-, mid-, and post-study.

Measure	Description
Diabetes Distress Scale (DDS)	The DDS is a 17-item instrument that assesses the emotional, physician-related, regimen-related, and interpersonal aspects of diabetes distress, and provides an indication of diabetes-related quality of life [13].
Diabetes Empowerment Scale - Short Form (DES-SF)	The DES-SF is a 28-item instrument used to measure psychosocial self-efficacy of diabetes self-management. This tool focuses on (1) managing diabetes, (2) assessing readiness to change, and (3) willingness to set goals and change behaviors [14,15].
Summary of Diabetes Self-Care Activities (SDSCA) measure	The SDSCA is a 11-item instrument that assesses individual levels of diabetes self-care, focusing on general diet, specific diet, exercise, medication adherence, blood-glucose testing, smoking, and foot care [16].
The Mobile Application Rating Scale (MARS) App - User Version	The MARS is a 26-item instrument used to evaluate the quality, functionality, and overall satisfaction of the mobile app itself [17].

### Sample Size

The sample size estimation was based on detecting a minimum reduction of 0.5% in A1c values. Given our inclusion criteria of A1c >7.5%, we anticipate that A1c levels will be highly clustered around 8.5% (standard deviation 1.0). A minimum of 63 participants per group is necessary to detect a difference of 0.5% in A1c, at an 80% power with a one-sided 5% significance level in all anticipated cases. With a further 15% adjustment for potential dropouts, a final sample size of 150 subjects will be required for both groups, with 75 participants in each study arm. All calculations were performed using the R software package, *epibasix* [18].

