### Data Analyses

The principal analysis strategy will be the use of linear mixed models in the Statistical Analysis System (Cary, NC, USA) using the PROC MIXED procedure. This approach provides a simple method to incorporate baseline values and the correlation of each participant over time (using a random effect). This model is more powerful than the repeated measures *analysis of variance*, as it can easily examine differences between the RCT groups at all time points, and can accommodate potential confounders. Furthermore, although the A1c measurements will be made at 3-month intervals, our primary analysis will focus on A1c levels at the conclusion of the 12-month study. A contrast will be constructed to test this primary comparison among all possible pair-wise tests; no adjustments for multiple testing will be required. Subsequent adjustments will be made for potential confounding variables as necessary, such as baseline parameters that may vary between groups (eg, age, sex).

Secondary contrasts will be used to examine differences from baseline for all other time points; however, these will be of exploratory interest only. Moreover, we will use regression analysis to separate the contribution of the different intervention components (activity monitor, weight scale, SMBG, mobile app features), and determine their independent effects on the primary outcome at 12 months. This approach will identify which aspect of the mHealth intervention contributed to the change in A1c.

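### The trial is sized on the SD of A1c levels while the primary outcome is change in A1c and the tested contrast is not fixed, so the claim of 80% power in every anticipated case is unsupported

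*Protocol article*

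**What the plan says.** Three sections of the protocol article bear on this.

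- **Outcomes:** "The primary outcome measure is change in A1c from baseline to 12 months".
- **Sample Size:** "The sample size estimation was based on detecting a minimum reduction of 0.5% in A1c values". The only SD is introduced by reference to the A1c entry criterion: "we anticipate that A1c levels will be highly clustered around 8.5% (standard deviation 1.0". From these inputs the section derives 63 per arm, and it words the power claim as follows: "at an 80% power with a one-sided 5% significance level in all anticipated cases". After a 15% dropout allowance the total is 150, 75 per arm. The section gives no SD of change, no 12-month SD and no baseline-to-12-month correlation, and it does not list the anticipated cases.
- **Data Analyses:** a linear mixed model is chosen partly because it can take in baseline values and within-participant correlation, and "our primary analysis will focus on A1c levels at the conclusion of the 12-month study". The section does not say whether baseline A1c enters as a covariate or as one of the repeated outcomes. Adjustment for baseline variables is described as a later step, taken if needed, with age and sex as the examples.

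**The concern.** The variance that determines power depends on the quantity tested. A difference in 12-month levels has the SD of levels. A difference in change has an SD that depends on r. A baseline-adjusted difference has a third SD. The protocol names change as the outcome, quotes an SD for levels and points the analysis at levels, and the wording of the model is compatible with all three contrasts.

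Two things are at stake. First, the power claim covers every anticipated case but rests on one SD for one quantity; for a change contrast it can fail by a wide margin if r is low. Second, the trial is unblinded, and a text that permits a change contrast, a level contrast or an adjusted contrast leaves a choice that should be closed before the data are seen.

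**Working it through.** **Inputs from the protocol article.** Difference 0.5, SD 1.0 (levels), 80% power, 5% labelled one-sided, 63 per arm, 15% dropout (all Sample Size); 1:1 allocation (Trial Design).

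**Assumptions, because the article gives no values.** The correlation r between baseline and 12-month A1c, and the 12-month SD. The main table takes the 12-month SD as 1.0.

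**Reproducing the plan's figure.** n per arm = 2 × ((z for alpha + z for power) × SD / difference)².

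- Two-sided 5%: 2 × ((1.960 + 0.842) / 0.5)² = 62.8, so 63. This matches.
- One-sided 5%: 2 × ((1.645 + 0.842) / 0.5)² = 49.5, so 50. This does not match the stated 63.
- Dropout: 63 / 0.85 = 74.1, so 75 per arm and 150 in total. This matches.

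Because 63 is the two-sided figure while the text says one-sided, both levels are shown below.

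**SD of each contrast, equal SDs of 1.0.**

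- Unadjusted level: 1.0 at any r.
- Change: √(2(1 − r)).
- Baseline-adjusted: √(1 − r²).

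**Power at 63 per arm, difference 0.5.** Noncentral t with 124 degrees of freedom and noncentrality 0.5 / (SD × √(2/63)).

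| r (assumed) | SD of change | Change, two-sided | Change, one-sided | Adjusted SD | Adjusted, two-sided |
|---|---|---|---|---|---|
| 0.3 | 1.18 | 65% | 76% | 0.954 | 83% |
| 0.4 | 1.10 | 72% | 82% | 0.917 | 86% |
| 0.5 | 1.00 | 79.5% | 87% | 0.866 | 89.5% |
| 0.6 | 0.89 | 88% | 93% | 0.800 | 94% |

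An unadjusted level contrast has 79.5% two-sided and 87.4% one-sided at every r. The 79.5% is the exact-t value; the normal approximation that yields 63 gives 80.1%.

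**Threshold for the change contrast.** Power of 80% needs an SD of change of at most 0.994 (two-sided) or 1.122 (one-sided). From r = 1 − SD²/2:

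- two-sided: 1 − 0.994²/2 = 0.51;
- one-sided: 1 − 1.122²/2 = 0.37.

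**Larger 12-month spread.** The entry criterion restricts A1c at baseline but not at 12 months, so a larger 12-month SD is possible. Take 1.2 with r = 0.5, both assumed.

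- Change: SD = √(1 + 1.44 − 2 × 0.5 × 1.2) = 1.114, power 71% two-sided and 81% one-sided.
- Adjusted: SD = 1.2 × √(1 − 0.25) = 1.039, power 76% two-sided and 85% one-sided.
- Unadjusted level: SD = 1.2, power 64% two-sided and 75% one-sided.

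**The case against.** The strongest reply is that Data Analyses names 12-month levels as the focus, and an SD of levels is the right input for a contrast of levels. On that reading the calculation is coherent: 87.4% power at the stated one-sided 5%, and 79.5% to 80.1% at two-sided 5%. This stands. It also rules out a stronger reading that a reader might infer, namely that 80% power is lost unless the contrast is baseline-adjusted. The documents do not support that. The level contrast essentially holds 80% if the 12-month SD is 1.0, and an unadjusted change contrast holds it once r reaches about 0.51 two-sided or 0.37 one-sided. The article gives no r, so nothing in it points to the unfavourable side. Above r = 0.5, the SD of levels is conservative for change.

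A second reply is that the mixed model already brings in baseline, and that the exact form is detail for a statistical analysis plan. With baseline A1c as a covariate, the arm difference in 12-month level and in change is the same estimate, so the two descriptions could be reconciled. This stands in part: an adjusted contrast may well be intended. But if baseline is a repeated outcome with its own mean in each arm, complete data give back the raw change or the raw level difference, depending on the contrast chosen. The article allows either. The point here is not a missing detail. It is a power claim, made without qualification, that rests on the SD of one quantity while the stated outcome is another.

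A third reply is that adjustment does not guarantee 80% either. That is correct, as the case with a 12-month SD of 1.2 shows at two-sided 5%.

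**Conclusion.** The point holds in a limited form. The outcome, the SD and the analysis focus refer to different quantities, and the claim of 80% power in all anticipated cases is not supported by anything shown. This does not establish that the trial is underpowered. For an unadjusted change contrast with SD 1.0 at both times, power runs from 65% at r = 0.3 to 88% at r = 0.6 two-sided (76% to 93% one-sided), so the claim fails for low r and is met for higher r.

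Fixing the baseline-adjusted contrast is worthwhile under either reading of the text. Two-sided, it gives 83% against 65% for change at r = 0.3, and 94% against 79.5% for level at r = 0.6. All these figures rest on assumed values of r and of the 12-month SD. This is a point that should be corrected; it does not threaten the design.

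**What to change.** - **Data Analyses:** define one primary estimate, the between-arm difference in 12-month A1c adjusted for baseline A1c. Either enter baseline A1c as a covariate with a baseline-by-visit term, or model baseline as an outcome with a common mean across arms. Say that this estimate is the one meant by the primary outcome in Outcomes.
- **Sample Size:** state the assumed r and 12-month SD. Show power for the chosen contrast over values of r on both sides of 0.5 and over more than one 12-month SD, at the significance level that will actually be used. Reconcile the one-sided label with the 63 per arm while doing so.
- Drop the statement that the power holds in all anticipated cases.

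**Cost:** wording in two sections and a small table. No extra patients and no new data are needed. The only downside is that the stated power becomes conditional on r and the 12-month SD.

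### The sample size paragraph states a one-sided 5% level, but 63 per group is what a two-sided 5% test needs; the stated level, power and N do not belong together

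*Protocol article*

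**What the plan says.** The Sample Size section gives all the inputs. On spread: "we anticipate that A1c levels will be highly clustered around 8.5% (standard deviation 1.0". On the target: "A minimum of 63 participants per group is necessary to detect a difference of 0.5% in A1c", and this is "at an 80% power with a one-sided 5% significance level in all anticipated cases". On attrition: "With a further 15% adjustment for potential dropouts, a final sample size of 150 subjects will be required for both groups", which is 75 per arm. The Trial Design section sets the randomisation "with a 1:1 allocation ratio".

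The Outcomes section defines the endpoint: "The primary outcome measure is change in A1c from baseline to 12 months". The Data Analyses section describes the primary test as a 12-month contrast from a linear mixed model: "A contrast will be constructed to test this primary comparison among all possible pair-wise tests; no adjustments for multiple testing will be required". It gives neither a significance level nor a direction for that contrast. The sample size sentence is therefore the only statement of either in the article.

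**The concern.** A sample size statement should reproduce from its own inputs. This one does not: 63 is larger than the stated level requires, and it equals the two-sided 5% figure.

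The mismatch bears on the decision rule for the primary outcome. If the sample size sentence is taken as fixing the test, the app could be declared superior on a one-sided 5% test. The chance of a false claim of benefit would then be 5%, twice the 2.5% implied by the level that yields 63. A worse A1c in the app arm could not be declared statistically significant. No reason is given for a one-sided test, and the trial is unblinded. A result falling between the two significance thresholds could be called positive or negative depending on which part of the paragraph is believed.

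**Working it through.** **Inputs**
- Difference δ = 0.5 A1c points, SD σ = 1.0, power 80%, level one-sided 5% (Sample Size)
- Equal allocation (Trial Design)
- Dropout 15% (Sample Size)

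**Formula.** For two independent means with equal arms, n per group = 2(σ/δ)²(z_α + z_β)². Here 2(1.0/0.5)² = 8 and z_β = 0.842.

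**Required n per group**

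| Level | Calculation | Normal approximation | Noncentral t |
|---|---|---|---|
| One-sided 5% (as stated) | 8 × (1.645 + 0.842)² | 49.5 → 50 | 51 |
| Two-sided 5% (one-sided 2.5%) | 8 × (1.960 + 0.842)² | 62.8 → 63 | 64 |

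The plan's 63 is the two-sided result.

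**Dropout step.** 63/(1 − 0.15) = 74.1 → 75 per arm, 150 in total. This agrees with the plan. From 50 or 51 per group the same step gives 59 or 60 per arm, so 118 to 120 in total.

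**Power at a given n.** Power ≈ Φ(δ/SE − z_α), with SE = σ√(2/n). At n = 63, SE = √(2/63) = 0.178 and δ/SE = 2.806.
- One-sided 5%: Φ(2.806 − 1.645) = 87.7% (noncentral t 87.4%)
- Two-sided 5%: Φ(2.806 − 1.960) = 80.1% (noncentral t 79.5%)

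With all 75 per arm evaluable, the figures are 92.2% one-sided and 86.5% two-sided.

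**Smallest significant observed difference at 63 per group**
- One-sided 5%: 1.645 × 0.178 = 0.29
- Two-sided 5%: 1.960 × 0.178 = 0.35

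**Could another route give 63 at one-sided 5% and 80% power?**
- A larger SD: 0.5 × √(63/2)/(1.645 + 0.842) = 1.13, which is not the stated 1.0.
- A change-score SD built from an SD of 1.0 at each visit, √(2(1 − ρ)): this equals 1.13 when ρ ≈ 0.36. The article gives no such correlation.

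Neither route uses figures in the article.

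**The case against.** The strongest reply has four parts.

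*The cause is inferred.* The SD of 1.0 describes A1c levels, whereas the endpoint is change from baseline, and the wording about all anticipated cases suggests that several scenarios were run and one printed. This stands in part. It is proven that the printed figures do not reproduce. That a two-sided calculation was mislabelled is the likeliest explanation, given the exact match, but it is not proven. The alternatives need inputs that the article does not state, so they do not rescue the sentence.

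*The direction of the primary test may be settled elsewhere.* The Data Analyses section is silent, and an analysis plan that is not shown may fix it. This too stands as a limit: a one-sided primary test is what this article allows, not something known to be planned. But such a plan could not make the sample size sentence correct.

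*A directional test fits the stated aim of detecting a reduction, and the model still estimates a difference in either direction.* Both are fair. A one-sided test is not wrong in itself. The fault is that its stated level does not match the N presented as its minimum, and that no justification is offered.

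*The design is not harmed, and the thresholds are approximate.* It is true that 150 is enough on either reading. The 0.29 and 0.35 figures assume an unadjusted comparison with SD 1.0; the mixed model's thresholds depend on correlations not given. This limits their precision. It does not affect the 5% against 2.5% error rate, which depends only on the level chosen.

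**Conclusion.** The concern holds. On the article's own inputs, one-sided 5% with 80% power needs 50 per group (51 by noncentral t), not 63. The stated 63 is the two-sided 5% figure. At 63 per group, power at the stated level is 87–88%, against 79.5–80% two-sided.

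These figures rest on a two-sample comparison with the stated SD of 1.0 applied to the endpoint. The consequence for the primary test further assumes that the level in the sample size paragraph governs it; nothing else in the article sets one. Because this leaves the decision rule for the primary outcome inconsistent with its own sample size, it must be corrected before the outcome is analysed. Enrolment is not in question.

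**What to change.** The sponsor should check its original calculation and reconcile level, direction, SD and n in the Sample Size section. Two corrections are open:

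- **If 63 is right, as the exact match suggests:** change the level to two-sided 5%. In Data Analyses, state that the 12-month primary contrast is tested two-sided at 5% and reported with a 95% confidence interval. The numbers stay at 63 evaluable per arm, 75 randomised per arm and 150 in total.
- **If one-sided 5% was truly intended:** give the reason, restate the minimum as 50 per group, and state the power at 63 as about 87%. State the same level and direction for the primary contrast.

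The analysis plan should carry the same wording. The cost is a text correction; the first option changes nothing in enrolment or conduct.
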